**Figure 4 F4:**
[figure not shown]
**Video-model explaining/demonstrating skills.** A Dutch actor explains how to recognize, dispute and replace irrational thoughts with rational thoughts, with the help of the 5G-schema.

#### **
*Providing information*
**

Providing information is used to increase participant’s knowledge, skills, and attitudes, using arguments and persuasive communication [44]. According to the elaboration likelihood model [106], good arguments are effective in reaching stable change in attitudes only when the message is processed through the central route. This happens when the message is personally relevant and not to discrepant from the participant’s beliefs [44]. The participant receives general (e.g. what are the dynamics of a bullying situation, what to do and not to do online) and tailored (e.g. questions that aid recognizing irrational thoughts and changing aggressive/passive coping into active and problem solving coping) information. To check whether the participant remembers the correct information, questions are asked interspersed with feedback. Additionally, to prevent the participant from paying attention to information (s)he already knows, at some points in the intervention (s)he can choose which information (s)he wants to read. Furthermore, all important information is summarized on the personal page and sent to the participant’s e-mail inbox.

#### **
*Modeling*
**

In modeling a person serves as an appropriate model for others that is reinforced for the desired behavior assuming that the behavior of the model will be imitated [107]. Modeling is included in this intervention as a method to increase participant’s self-efficacy and behavioral capability to carry out the desired behavior change, because it is proven to be an effective teaching tool [108]. For example, previous research indicated that video-counseling - in which a real human speaks and asks questions - can be a promising technique for health interventions [109]. In line with the parameters of modeling, the video-models are coping models (i.e. who previously experienced the health problem, but who learned to deal with it effectively), the participant is able to identify with the models, and the models are being reinforced for positive behavior [44]. The short videos were professionally recorded [110]. In several video-clips, models demonstrate and explain how to perform a behavior (e.g. recognizing, disputing and replacing irrational thoughts, coping behaviors).

#### **
*Implementation intentions and coping plans*
**

Research indicates that planning is a powerful self-regulatory tool in the process of behavior change [111,112]. When people plan, they mentally simulate the linking of concrete responses to future situations, replacing spontaneous reactions for pre-planned actions. There are two types of plans: action plans [113], or implementation intentions [114], and coping plans [112]. In action planning, individuals link goal-directed behavior to certain environmental cues by specifying when, where and how to act [112] in if-then statements [115]. As a result, environmental cues should activate - without conscious intent - the initiation of action [112]. In coping planning, individuals anticipate on possible risk situations beforehand by already defining suitable and effective response behavior linked to these potential barriers [112]. Implementation intentions, action and coping plans are found to be effective in translating various intentions into actions [116-118], and appear to be working synergistically in adolescents [119]. In the intervention, the participant makes a combination of implementation intentions and coping plans. A closed-ended plan setting procedure is used to prevent inadequate goals; from a predefined list, the participant chooses the context *if* (either difficult situations or situations in daily life) and action *then* (applications of learned skills, from a predefined list).

### Step 4: Producing program components and materials

Taking the end products of the previous steps into account, we decided to develop one intervention containing three web-based sessions containing tailored pieces of advice addressing mostly personal and psychological determinants. A program plan including the scope, sequence and program materials was developed [44], which is described below. During the process of producing program components and materials, intended program participants and the Linkage group were consulted to determine the preferences for program design by conducting focus group interviews and short voting sessions.

#### **
*Scope and sequence*
**

Based on brainstorms and voting sessions with members of the target group, we named the intervention *Online Pestkoppenstoppen* with three web-based tailored pieces of advices named: (1) *Think strong, feel better*; (2) *Stop the bully now!*; and (3) *You are doing great, can you do better?*. Each advice is preceded by several questionnaires – measuring tailoring and effect variables - that take approximately half an hour to complete, and each advice takes approximately 45 minutes to complete. The pieces of advice are offered divided over three months, and e-mails and text messages are used to remind the participant of participation (see Figure 5). The intervention can be found and is accessed on http://www.pestkoppenstoppen.nl.

**Figure 5 F5:**
[figure not shown]
**Flowchart of the web-based tailored advices and questionnaires.** Questionnaires precede each advice, and are used to tailor the advices to the characteristics of each participant. The questionnaires are also used to do the effect evaluation. Each advice consists out of lessons aimed at teaching different skills.

#### **
*Selection*
**

Because the literature indicates that an explicit approach (e.g. ‘did you experience cyberbullying?’) systematically underestimates the problem [47,58], an implicit approach was used; the individual rates his or her experience with different cyberbullying behaviors. Individuals are included in the intervention if they had experiences with at least one of the cyberbullying behaviors at least ‘once a month’ during the last half year. Cyberbullies and adolescents who did not experience the 17 deviant cyberbehaviors are excluded from participation. Next, the individual (=participant) fills in his or her (nick)name, age, e-mail address, mobile phone number and a login code that is provided to him/her in an information letter. The e-mail address and mobile phone number will be used to remind participants of participation before the start of each advice, during the process of filling in the questionnaires, and during the process of completing each advice.

#### **
*Materials*
**

Below, we shortly describe the different materials developed for the intervention.

#### **
*Personal page*
**

After selection/logging in, the participant is redirected to the personal page, from which (s)he: (1) can proceed or continue with the questionnaires and/or pieces of advice; (2) can find for each advice pictures, video-clips, comics, summaries, formed helpful thoughts, plans and sentences to use; and (3) has access to the extra tailored social skill lessons of advice 2.

#### **
*Assessing tailoring and effect measures*
**

Before receiving each web-based tailored advice, the participant answers several questionnaires (T0, T1 and T2) to assess the effect and tailoring variables. Gender of the participant was used to tailor gender of the guides and contexts (e.g. girls will see Noa, Jessica and a girl’s bedroom, and boys will see Levi, Mike and a boy’s bedroom).

#### **
*Advice 1.‘Think strong, feel better.’*
**

After the baseline measure (T0), the participant starts with the first advice. The participant learns to: (1) work with the 5G-schema in order to recognize (PO 1), dispute (PO 2) and replace (PO 3) irrational thoughts with rational thoughts; (2) carefully examine emotions in response to certain events (PO 4); and (3) form action plans to use the 5G-schema in daily life (PO 10).

#### **
*Advice 2 ‘Stop the bully now!’*
**

A month after the start, the participant begins with the second questionnaire (T1) and advice. The participant: (1) receives knowledge about the dynamics of online and offline bullying situations; (2) receives general APS coping strategies (PO 6); (3) learns and forms implementation intentions for responding towards online and offline bullying (PO 7 and PO 10); (4) becomes aware of ineffective coping style (PO 5); (5) is offered tailored examples of and guidance in APS coping (PO 6 and 7); (6) learns about responding assertively (PO 8 and 9); (7) forms implementation intentions and coping plans regarding assertive responses (PO 10); and (8) receives information about the use and benefits of humor and bystanders (PO 6). Observing victimization on its own can have negative consequences on psychological wellbeing [120]. Therefore, the participant forms implementation intentions and coping plans regarding how to react and involve bystanders in (cyber)bullying situations (PO 10).

#### **
*Additional lessons*
**

Additional social skill lessons (PO 7 and 9) were offered to improve specific skills associated with problem behaviors that are tailored to the participant’s score on several Youth Self-Report (YSR) scales [121]. The participant can choose if, when and which extra lessons (s)he wants to complete. For several extra lessons implementation intentions and coping plans are formed (PO 10). An overview of all lessons tailored to norm scores (above the 93% clinical range on YSR subscales) can be found in Table 1.

**Table 1 T1:** Social lessons based on YSR subscales with norm scores for gender

	**YSR social problems**		**YSR withdrawn/depressed**		**YSR aggression**	
	**Male > 7**	**Female > 7**	**Male > 6**	**Female > 7**	**Male > 12**	**Female > 13**
Starting conversations	X	X	X	X		
Asking questions	X	X	X	X		
Express feelings and opinions	X	X	X	X		
Empathy/social cognition	X	X			X	X
Non-verbal communication	X	X				
Planning to become more socially active			X	X		
Emotional regulation					X	X

Lessons are offered when the participant scores above the 93% clinical range, as can be found in the YSR manual. Norm scores are different for males and females.

#### **
*Advice 3 ‘You are doing great, can you do better?’*
**

Two months after the start, the participant starts with the third questionnaire (T2) and follow up advice. The participant evaluates all plans made in advice 1 and 2 on usability, and if necessary adjusts the plans (PO 10). All skills of advice 1 and 2 are summarized into three steps (i.e. 1. Think; 2. Act; 3.Closure). These three steps together form the skill conflict resolution, which is associated with reductions in victimization and fewer internalizing problems [90]. Tailored on progress, the participant receives feedback (on irrational thoughts, coping responses and YSR scores) and if needed additional lessons (5G-schema, coping styles, humor, non-verbal communication and emotion regulation). Finally, the participant learns and plans how to use the Internet and mobile phone in a safe and secure manner (PO 11).

#### **
*Development*
**

The web-based tailored pieces of advice were developed using special software (Nettailor, Evident, the Netherlands), a program that has been developed specifically for web-based tailored interventions, using digital guides in the delivery of the intervention. Research indicates that the integration of an intervention into a website enhances participants’ outcomes and retention [40]. Therefore, the web-based tailored pieces of advice were integrated into a website (http://www.pestkoppenstoppen.nl) (see Figure 6). On this website information about the intervention can be found. After logging in, participants can read general information and watch YouTube video clips about (cyber)bullying, follow the web-based tailored pieces of advice and/or answer the questionnaires.

**Figure 6 F6:**
[figure not shown]
**The website ****
*Online Pestkoppenstoppen.*
**

#### **
*Pretest of the interventions*
**

Parts of the focus group interviews conducted for the development of this intervention were pre- and pilot tests. Members of the target group were instructed to go to the website, complete the questionnaires and follow the pieces of advice. Next, six focus group interviews were held with a total of 41 participants from 4 schools. Based on the results from the pretests, pilot tests and focus group interviews, several adjustments were made: lay-out issues were resolved, bugs were repaired and both the number of questions and the amount of content were reduced.

### Step 5: Adoption and Implementation

A plan for the adoption, implementation and continuation of the web-based tailored intervention was developed. To facilitate adoption and implementation, a linkage group was formed [44]. The intervention was developed in such a way that the potential for adoption, implementation and continuation is enhanced. For example, intervention users can find, register and use the intervention online. Therefore, the implementation of the intervention does not need additional human actions. The only actions needed and costs associated with the implementation, adoption and continuation are recruiting participating schools or individuals, hosting the website, preparing the intervention for implementation after the research has been conducted, and keeping the information up-to-date. Hence, the intervention can easily reach a large number of adolescents and at very low costs.

### Step 6: Planning for evaluation

The evaluation of the program - which is described below - was planned. The research on the effectiveness of the intervention *Online Pestkoppenstoppen* has been approved by the Medical Ethics Committee of the Atrium Hospital of Heerlen (NL39072.096.12; METC nr. 12-T-126), and is registered in the Dutch Trial Register (http://NTR3613).

#### **
*Design and procedure*
**

A three-group (experimental group, general information group and waiting list control group) randomized control trial (RCT) will be conducted to evaluate the efficacy of the intervention, with self-assessed measures at baseline (T0), before advice two (T1), before advice three (T2), a half-year post start (T3) and 1 year post start (T4) (see Figure 7). Statements about the effectiveness of the three tailored web-based pieces of advice compared to general information can be made by comparing the experimental group with the general information group. The waiting list control group allows for controlling internal validation issues such as aging. However, this group does not receive measurements at T4. After the research, both the waiting list control group and general information group will be allowed to use the intervention.

**Figure 7 F7:**
[figure not shown]
Timing and distribution of the measuring moments between the three conditions.

Participants will be recruited via contacting all secondary vocational education schools in the Netherlands. When schools give their consent to participation, randomization will follow. Schools will be stratified on three categories; a) size (small, medium or large); b) location of school (urban or rural); and c) type of education (theoretical or both theoretical and vocational). Schools will be matched and randomly assigned to one of the three intervention conditions. After randomization, all participants will attend a lesson at school in which the research will be explained. Participants receive a written information letter and informed consent, which has to be signed by both the participant and his or her parent(s). Next, participants have to visit the website and complete the selection questionnaire. When a participant meets the inclusion criteria, registration will follow and the research and intervention procedure will start.

A back-up plan was created in case the above-mentioned method of recruiting did not provide a sufficient number of participants. In case of insufficient participants, adolescents are recruited by placing a message on several popular websites often visited by adolescents and/or their parents. Additionally, recruitment messages are sent via Facebook, LinkedIn and Twitter. In this message individual adolescents are recruited to participate in the research by asking them to send us an e-mail with their name, age, name of school and level of education. Next, they receive instructions (written and on video), a written information letter and informed consent for them and their parents. In case parents read the message, they are asked to let their child participate in the research. Only after the adolescent provides us with the signed informed consents from them and their parents, will a login code be sent to the participant with which (s)he can access the intervention and/or research.

#### **
*Measurement instruments*
**

To evaluate the effectiveness of the intervention, several concepts will be measured via self-reported questionnaires. The primary outcomes of this study are frequency of (cyber)bullying, psychological wellbeing, problem behavior, school performance and truancy. These will be assessed at baseline (T0), 6 (T3) and 12 months (T4) follow-up. The secondary outcomes of this study (i.e. moderators or working mechanisms (mediators) of the intervention) are irrational thoughts, self-efficacy, coping with cyberbullying and self-esteem. These will be assessed at baseline (T0), after 1 (T1), 2 (T2), 6 (T3) and 12 months (T4) follow-up. At baseline, several moderators will be measured as well (i.e. demographic characteristics such as gender, age, educational level). In addition, a process evaluation at T3 will be conducted to examine potential moderators.

#### **
*Power calculation*
**

The power analysis is based on two important dependencies: decrease in psychosocial problems and the amount of cyberbullying victims after the intervention. The outcomes are based on the PaS training [122]. A power calculation (effect size = .3; power = .80; intracluster correlation coefficient = .1) showed that at baseline about 446 participants were needed (based on a dropout rate of 20%). Based on previous studies we suspect that 25% of the adolescents between 12 and 15 years can be classified as cyberbullying victims, and that 50% of the adolescents are willing to participate. This results in 3570 adolescents, divided over 30 schools, with each school having 4 or 5 classes.

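### School route: pupils are informed, consented, screened and measured at T0 after their school is randomised, with no described step hiding the arm, so recruitment bias is possible

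*Protocol article*

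**What the plan says.** Under Step 6, Design and procedure, the order for the school route is explicit.

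- Randomisation comes straight after the school agrees: "When schools give their consent to participation, randomization will follow".
- The unit is the school: "Schools will be matched and randomly assigned to one of the three intervention conditions". Stratification uses three school characteristics: size, urban or rural location, and type of education.
- Pupils hear about the study next: "After randomization, all participants will attend a lesson at school in which the research will be explained". They then receive a letter and a consent form, to be signed by pupil and parent(s).
- Screening follows: "Next, participants have to visit the website and complete the selection questionnaire".
- Entry comes last: "When a participant meets the inclusion criteria, registration will follow and the research and intervention procedure will start".

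Step 4 adds two facts. Eligibility rests on the pupil's own ratings: "Individuals are included in the intervention if they had experiences with at least one of the cyberbullying behaviors", with a minimum frequency of once a month over the past half year. T0 sits directly before the programme content: "After the baseline measure (T0), the participant starts with the first advice".

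The Power calculation section expects 25% of adolescents to be victims and 50% to be willing to take part, with no split by arm.

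**The concern.** Randomising schools makes the schools comparable. It does not by itself make the recruited pupils comparable, because every step that decides which pupils are analysed happens after the school's arm is drawn. If the school, the person giving the lesson, the pupils or the parents know the arm by then, two things can differ between arms: the decision to join, and the answers on the selection questionnaire.

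This trial has features that leave room for both.

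- Joining needs active consent from pupil and parent(s), and half of the pupils are expected to decline.
- Incentives differ in timing. Experimental pupils get the tailored programme at once. The other two groups may use it only after the research, while still completing long questionnaires.
- The entry criterion is self-reported cyberbullying experience, and the frequency of (cyber)bullying is also a primary outcome. Reporting that depended on arm at screening would therefore select on the outcome itself.
- All outcomes are self-reported, so no independent measure would reveal such an imbalance.

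Stratifying or matching on school size, location and type of education does not balance who volunteers inside a school. A larger sample would not remove the bias either.

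**Working it through.** **1. Order of steps.** Taking Step 6 and Step 4 together: school consent, randomisation, lesson, letter with pupil and parent consent, selection questionnaire, registration, T0, advice 1. Everything from the lesson onward follows allocation. The article mentions no concealment of the arm at recruitment, no list of eligible pupils drawn up beforehand and no baseline before allocation.

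**2. The plan's own uptake figure.** 446 / (0.25 × 0.50) = 3568, against 3570 stated. So the target rests on 50% uptake, one figure for all arms, with 12.5% of approached adolescents (0.25 × 0.50) entering the trial.

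**3. Illustration of size.** The documents give no uptake by arm, so the following inputs are assumptions. Willingness to join is a standard normal trait, pupils above a threshold join, and the trait correlates r = 0.2 to 0.4 with the outcome. With uptake p and threshold z, the mean trait among joiners is φ(z)/p. The spurious difference is r times the difference in these means.

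| Uptake | φ(z) | Mean trait, higher-uptake arm | Mean trait, lower-uptake arm | Difference | × 0.2 | × 0.4 |
|---|---|---|---|---|---|---|
| 50% v 50% | – | equal | equal | 0 | 0 | 0 |
| 55% v 45% | 0.396 | 0.396/0.55 = 0.720 | 0.396/0.45 = 0.880 | 0.160 | 0.032 SD | 0.064 SD |
| 60% v 40% | 0.386 | 0.386/0.60 = 0.644 | 0.386/0.40 = 0.966 | 0.322 | 0.064 SD | 0.129 SD |

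Against the planned effect of 0.3, the 55% v 45% case is 0.032/0.3 = 11% to 0.064/0.3 = 21%. The 60% v 40% case is 21% to 0.129/0.3 = 43%. The direction depends on the sign of the correlation, so the bias could inflate or mask an effect.

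**4. Effect of adjusting for T0.** Assume further that the trait relates equally to the T0 and follow-up values of the outcome, that these two correlate 0.5 to 0.7, and that T0 answers are not themselves influenced by the arm. The residual bias is then (1 − correlation) × the raw figure.

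- 55% v 45%: from 0.3 × 0.032 = 0.01 SD to 0.5 × 0.064 = 0.03 SD.
- 60% v 40%: from 0.3 × 0.064 = 0.02 SD to 0.5 × 0.129 = 0.06 SD, or about 6% to 21% of 0.3.

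If T0 answers are influenced by the arm, or the selecting trait acts mainly on later outcomes, adjustment removes less than this.

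**The case against.** The strongest reply is that the order of steps alone does not create bias; knowledge of the arm does. A reader might infer that the lesson or letter tells pupils which arm their school is in. The article does not say so. It says only that the research is explained. Masking at recruitment and the wording of the letter are details that a condensed article commonly leaves to the full protocol, which is not shown. If all arms receive the same letter and lesson and the arm appears only after T0, most of the mechanism disappears. This stands, and it limits the point to a risk.

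Second, Design and procedure bases statements about effectiveness on the experimental group against the general information group. The waiting list serves to control for matters such as ageing and has no T4 measurement. Both groups in the main contrast are offered content during the trial, and all arms may use the intervention afterwards. A large gap in uptake is therefore more plausible against the waiting list than in the main contrast. This also stands.

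Third, a reader might infer that T0 is useless because it follows allocation. That goes too far. T0 precedes advice 1 and includes the primary outcomes, so adjustment would remove part of any imbalance in measured severity.

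Fourth, over-reporting of victimisation to gain entry is speculative: pupils rate specific behaviours on a website, and nothing says they are told the threshold.

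None of these replies removes the written sequence, which leaves validity dependent on a safeguard that the article does not describe.

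**Conclusion.** The point holds as a design risk in the school route, and should be fixed. The sequence is certain, because the article states it. The bias is conditional: it needs the arm to be known before T0 closes, and uptake or reporting to respond to it.

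On the assumed uptake and correlation values, the size is about 0.03 to 0.06 SD for a ten-point gap in uptake and 0.06 to 0.13 SD for a twenty-point gap, before T0 adjustment and against a target of 0.3. It is zero if uptake does not depend on arm. The risk is probably largest against the waiting list and smaller in the main contrast with general information.

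The documents do not support the stronger conclusion that the comparison is biased, or that the trial cannot be interpreted unless the order is changed. The point also does not extend to the back-up route, in which individuals answer web messages and consent before receiving a login code. The article does not describe how they are allocated.

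**What to change.** In each school, complete the lesson, pupil and parent consent, the selection questionnaire and T0 before the allocation is drawn. Schools can be matched and randomised in batches once T0 has closed for the batch. If that order is impracticable, the minimum is to withhold the allocation from the school, the lesson-givers, pupils and parents until T0 has closed. In either case use one neutral information letter and one lesson script for all three arms, and state in the protocol who knows the arm at consent, screening and T0.

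The cost is a change in the order of procedures and an ethics notification, with no added measurements. Each batch of schools waits a short time for its allocation. Advice 1 also starts slightly later after T0, so the T0 answers used for tailoring are somewhat older when the advice is given.

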This intervention has a number of limitations. First, it was difficult to reduce the number of questions in the questionnaires we used for evaluation purposes. In the focus group interviews, members of the target group clearly stated that too many questions will lead to drop-out, because answering many questions is experienced as boring and fatiguing. Furthermore, too many questions may cause no-saying or yes-saying and response fatigue (for a review, see [123]), leading to less reliable results. Second, the intervention may contain too much information. Based on the literature, it was decided to include the 5G-schema, coping strategies, social skills, planning and safety instructions. In focus group interviews, members of the target-group mentioned the large amount of information making it difficult to remember everything. Third, we cannot exactly check the degree of usage on the experimental and general information. This may hamper the interpretation of the results. Therefore, we have added process evaluation questions, in which we ask the participants if they have read the information.

In conclusion, the *Online Pestkoppenstoppen* program seems to be a promising start in solving current cyberbullying problems. The results of the evaluation studies, which will be reported in other papers, may contribute to the knowledge about how to stop online victimization and how to use tailoring and web-based interventions in this purpose. Additionally, this intervention may also affect offline victimization, because despite the differences, cyberbullying and traditional bullying also have some overlapping characteristics [24,25,27]. The results can be used as input for other web-based and computer-tailored interventions aimed at cyberbully victims. If the studies point out that the intervention is effective in its purpose, we have an intervention ready for implementation on a large scale.

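### The T3 process evaluation is planned as a source of moderators although it is measured after treatment; treatment effects split by such variables can be biased in either direction

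*Protocol article*

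**What the plan says.** Under Step 6, Measurement instruments, the protocol article lists two sources of moderators. The first is measured before treatment: "At baseline, several moderators will be measured as well (i.e. demographic characteristics such as gender, age, educational level"). The next sentence adds a second: "In addition, a process evaluation at T3 will be conducted to examine potential moderators".

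The timing is fixed elsewhere. Step 6, Design and procedure, lists the later measurements as "before advice three (T2), a half-year post start (T3) and 1 year post start (T4"). Step 4, on Advice 3, says: "Two months after the start, the participant starts with the third questionnaire (T2) and follow up advice".

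The Discussion gives the process evaluation two further roles. Among the strengths, it is said to permit conclusions on working mechanisms, a term that Measurement instruments equates with mediators. Among the limitations, the article admits that "we cannot exactly check the degree of usage on the experimental and general information", and continues: "Therefore, we have added process evaluation questions, in which we ask the participants if they have read the information".

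**The concern.** A moderator analysis asks whether the treatment effect differs between kinds of participant. The answer has the protection of randomisation only if the characteristic was settled before treatment could influence it. Answers given at T3 come after the advices. Whether and how a pupil engaged may depend on the arm, on motivation, and on how the pupil was already faring. Pupils who give the same answer in two arms may then differ in prognosis, and the difference between arms within that subgroup mixes the treatment effect with that imbalance.

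The three roles (moderator, mediator, usage check) also call for different analyses. An effect that appears confined to engaged pupils could be reported as effect modification when the true effect is the same for everyone.

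**Working it through.** **Order of measurement.** The third advice starts at 2 months and T3 is at 6 months, so the process evaluation comes 6 − 2 = 4 months after the last advice begins. It coincides with the first follow-up of the primary outcomes, which are measured again at T4.

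**Can this create false moderation?** The article gives no reading rates and no correlations, so everything below is assumed except the effect size of 0.3, which comes from the power calculation. Reading is used as the example because it is the only process item the article names.

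Model: 2,000,000 participants in two arms (A = 1 experimental, A = 0 comparison), with a latent trait U ~ N(0,1).
- Outcome: Y = d·A + 0.5·U + √0.75·e, so Y has SD 1 within each arm and the effect d is the same for everyone.
- Reading: log-odds = a·A + b·U, where the slope b may differ by arm.
- False moderation = (arm difference in readers) − (arm difference in non-readers). Its true value is 0.

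| d | a | b experimental | b comparison | Effect, readers | Effect, non-readers | False moderation |
|---|---|---|---|---|---|---|
| 0.3 | 0 | 0 | 0 | 0.302 | 0.302 | 0.001 |
| 0.3 | 0 | 0.5 | 0.5 | 0.299 | 0.302 | −0.003 |
| 0.3 | −0.5 | 0.5 | 0.5 | 0.333 | 0.328 | 0.005 |
| 0.3 | −0.5 | 1 | 0.25 | 0.488 | 0.195 | 0.293 |
| 0.3 | 0.5 | 0.25 | 1 | 0.139 | 0.426 | −0.286 |
| 0 | −0.5 | 1 | 0.25 | 0.189 | −0.103 | 0.292 |

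(Last digits may differ by 0.001 because of rounding.) Adding selective non-response to the fourth row, with 78.2% responding, gives 0.487, 0.201 and 0.286. Missing answers are therefore not what drives the result.

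**A case with biased subgroups but almost no false moderation.** Take a true effect of 0 and Y = 0.4·U + noise, with a pupil reading if U + N(0,1) > c, where c = 0 (experimental, 50% readers) and c = 1 (general information, 24% readers). With z = c/√2, the mean of Y is 0.4·(1/√2)·φ(z)/(1 − Φ(z)) in readers and −0.4·(1/√2)·φ(z)/Φ(z) in non-readers.
- Readers: 0.226 − 0.366 = −0.14.
- Non-readers: −0.226 − (−0.116) = −0.11.
- False moderation: −0.14 − (−0.11) = −0.03.

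Both subgroup effects are wrong, since the truth is 0, yet the contrast between them is close to nil. A large false interaction needs the process variable to relate to prognosis differently in the two arms.

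**The case against.** The strongest reply is that this is an exploratory side analysis in an article mainly about developing the intervention. Mediators are properly measured after treatment, so moderator may simply be the wrong word in one sentence. How moderators are modelled belongs in an analysis plan that is not shown. Much of this stands: the main comparison is untouched, and the baseline moderators remain sound. It does not remove the point, because the article itself states that moderators will be sought in T3 data, directly after listing those measured at baseline.

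A reader might infer more than the article supports:
- **That any such analysis is biased.** The first two rows of the table show none, and the third shows about 0.03 SD in each subgroup with no false moderation.
- **That reading will be the moderator.** This follows only from joining Measurement instruments with the Discussion, where reading is asked about as an aid to interpreting usage.
- **That the analysis is confined to responders.** The article assumes 20% dropout (446 × 0.80 ≈ 357 with follow-up, if that rate applied at T3), but this affects every follow-up measure and its handling may be set out elsewhere.
- **That lack of process data in the waiting list spoils the comparison.** The effectiveness contrast named in Design and procedure is experimental versus general information, and the Discussion's remark on usage covers both of those groups.
- **That the trial promises conclusions on what works for whom.** Similar words in the Background describe a general standard for interventions.
- **That self-report is the only usage measure although full logs exist.** Reminders are sent "before the start of each advice, during the process of filling in the questionnaires, and during the process of completing each advice", which suggests that some completion status is held. Its content, its coverage of the general information group and whether it can be exported are unknown. The article says only that usage cannot be checked exactly.

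**Conclusion.** The point holds in a limited form. The article labels variables measured at T3 as potential moderators and elsewhere gives the same evaluation the role of evidence on mechanisms. Treatment effects split by these variables have no randomised interpretation and can be biased in either direction. Under the assumed reading models, false moderation runs from about 0 to about 0.3 SD in absolute size, so at worst it matches the effect size of 0.3 in the power calculation. Where in that range the trial would fall depends on whether the process variable relates to prognosis differently by arm, and the article gives no information on that. The main randomised comparison and the moderator analyses on baseline characteristics are unaffected, so this is a worthwhile correction of limited weight.

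**What to change.** - In Measurement instruments, restrict moderator (effect-modification) analyses to variables measured at T0.
- Describe the T3 process evaluation, including self-reported reading, as descriptive or exploratory data on adherence or mechanism, and state that subgroups formed on it carry no randomised interpretation.
- Give the evaluation the same role in Measurement instruments and in the strengths and limitations of the Discussion.
- Where the website holds completion status, show it beside self-reported reading. Opening a page does not prove that it was read, so neither measure replaces the other.

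The cost is a few sentences and, if completion records exist, an export of them. The downside is that no moderator claims can be made from process variables. An estimate of the effect of actual use would need assumptions of its own, not least because use means different material in the experimental and general information groups, and it is not needed to resolve this point.
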